## Abstract

**Background:**

BRCA1 and BRCA2 genes are critical in homologous recombination DNA repair and have been implicated in familial breast and ovarian cancer tumorigenesis. Tumour cells with these mutations demonstrate increased sensitivity to cisplatin and poly (ADP-ribose) polymerase (PARP) inhibitors. 6MP was identified in a screen for novel drugs and found to selectively kill BRCA-defective cells in a xenograft model as effectively as the PARP inhibitor AGO14699, even after these cells had acquired resistance to a PARP inhibitor or cisplatin. Exploiting the genetic basis of these tumours enables us to develop a more tailored approach to therapy for patients with BRCA mutated cancers.

**Methods:**

This multi-centre phase II single arm trial was designed to investigate the activity and safety of 6-mercaptopurine (6MP) 55 mg/m^2^ per day, and methotrexate 15 mg/m^2^ per week in patients with advanced breast or ovarian cancer, ECOG PS 0–2, progressing after ≥ one prior regimen and known to bear a BRCA1/2 germ line mutation. Accrual was planned in two stages, with treatment continuing until progression or unacceptable toxicity; in the first, if less than 3/30 evaluable patients respond at 8 weeks after commencing treatment, the trial will be stopped for futility; if not, then accrual would proceed to a second stage, in which if more than 9/65 evaluable patients are found to respond at 8 weeks, the treatment will be regarded as potentially effective and a phase III trial considered subject to satisfactory safety and tolerability. The primary outcome is objective response at 8 weeks, defined by RECISTS v1.1 as complete response, partial response or stable disease. Secondary outcomes include safety, progression- free and overall survival, and quality of life.

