**Discussion:**

This study aims to investigate whether 6MP might be an effective treatment for BRCA deficient tumours even after the development of resistance to PARP inhibitors or platinum drugs. The study has surpassed the first stage analysis criteria of more than 3 out of 30 evaluable patients responding at 8 weeks, and is currently in the second stage of recruitment.

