### Sample size determination and power

The 6MP study aims to recruit 30 evaluable patients in the first stage, and 65 patients in total. The Simon compromise/admissible two-stage design [15, 16] was implemented to calculate this required sample size to detect an increase in response rate from 10% to 20%, with a power of 90% and a significance level of

20%. In the first stage of the study, if fewer than 3 out of 30 evaluable patients respond at 8 weeks after first treatment, then the trial will be stopped for futility; if 3 or more respond then a further 35 patients will be recruited in the second stage. If nine or more of the total 65 patients respond at 8 weeks then the treatment will be regarded as potentially effective and a phase III randomised trial will then be considered, if, in addition, the treatment appears to be safe and well tolerated, and the trial roll-out over multiple centres proves feasible.

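### The final success threshold is at least 10 of 65 in the Abstract but at least 9 of 65 in the sample size section, and only the latter gives the stated 90% power

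*Protocol article*

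**What the plan says.** Final decision:

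- Abstract, Methods paragraph: "in which if more than 9/65 evaluable patients are found to respond at 8 weeks, the treatment will be regarded as potentially effective". More than 9 means 10 or more.
- Sample size determination and power: "If nine or more of the total 65 patients respond at 8 weeks then the treatment will be regarded as potentially effective". This means 9 or more.

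Stage 1 decision:

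- Sample size determination and power: "if 3 or more respond then a further 35 patients will be recruited in the second stage". The trial stops with 2 or fewer.
- The Abstract's Methods paragraph agrees: it stops the trial below 3 of 30.
- The Abstract's Discussion paragraph reports that the study has "surpassed the first stage analysis criteria of more than 3 out of 30 evaluable patients responding at 8 weeks", which read literally is 4 or more.

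Design targets, given only in the sample size section: "The Simon compromise/admissible two-stage design", response rates of 10% and 20%, "with a power of 90% and a significance level of" 20%, with 30 evaluable patients in stage 1 and 65 in total.

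**The concern.** The count of responders among 65 is the only efficacy hurdle between this single-arm trial and consideration of phase III. Two published thresholds one patient apart mean that a result of exactly 9 has no fixed interpretation, and that the reading could be chosen after the count is known. The two rules also have different error rates, so at most one of them need match the stated design. The stage 1 wording raises the same question on a smaller scale: whether exactly 3 responders would have been enough to continue.

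**Working it through.** **Inputs** (all from Sample size determination and power unless noted): n1 = 30, n = 65, so n2 = 35; p0 = 0.10; p1 = 0.20; power 90%; significance level 20%. Sidedness is not stated; I take it as one-sided, as is usual for a Simon design, and treat 20% as an upper limit.

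**Formula.** With c1 the minimum number of stage 1 responders needed to continue and c the minimum total needed for success,

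P(success | p) = Σ over x ≥ c1 of P[Bin(30, p) = x] × P[Bin(35, p) ≥ c − x].

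At p = 0.10 this is the type I error; at p = 0.20 it is the power.

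**Reproducing the stated power (c1 = 3, c = 9), with c = 10 alongside, at p = 0.20:**

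| Stage 1 responders x | P(x) | P(stage 2 ≥ 9 − x) | P(stage 2 ≥ 10 − x) |
|---|---|---|---|
| 3 | 0.0785 | 0.7279 | 0.5672 |
| 4 | 0.1325 | 0.8565 | 0.7279 |
| 5 | 0.1723 | 0.9395 | 0.8565 |
| 6 | 0.1795 | 0.9810 | 0.9395 |
| 7 | 0.1538 | 0.9960 | 0.9810 |
| 8 | 0.1106 | 0.9996 | 0.9960 |
| 9 | 0.0676 | 1 | 0.9996 |
| 10 or more | 0.0611 | 1 | 1 |

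Multiplying across and summing gives 0.901 for c = 9 and 0.847 for c = 10.

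**All four combinations of the published wordings:**

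| Continue if | Success if | Type I error | Power | Meets 20% and 90%? |
|---|---|---|---|---|
| ≥ 3/30 | ≥ 9/65 (sample size section) | 0.183 | 0.901 | yes |
| ≥ 3/30 | ≥ 10/65 (Abstract, Methods) | 0.106 | 0.847 | no, power |
| ≥ 4/30 | ≥ 9/65 | 0.152 | 0.844 | no, power |
| ≥ 4/30 | ≥ 10/65 | 0.093 | 0.802 | no, power |

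**Can another stage 1 boundary rescue the Abstract's threshold?** No. With no interim stop at all, P[Bin(65, 0.20) ≥ 10] = 0.863, and any futility stop can only lower this.

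**Stage 1 stopping when the true rate is 20%:** P[Bin(30, 0.20) ≤ 2] = 4.4%; P[Bin(30, 0.20) ≤ 3] = 12.3%.

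**How often the two final rules disagree.** They differ only if stage 1 is passed (≥ 3/30) and the total is exactly 9. That probability is the difference between the two success probabilities:

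- true rate 10%: 0.1831 − 0.1057 = 0.077
- true rate 15%: 0.6216 − 0.5004 = 0.121
- true rate 20%: 0.9009 − 0.8468 = 0.054

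**The case against.** The sample size section is the authoritative statement. It is the only place that gives power and significance level, and its own rule delivers them. On this view the design is sound, and the Abstract merely writes more than where at least was meant. That is a fair account of the probable origin, and it stands: the sample size calculation itself is not wrong. It does not remove the conflict, because the Abstract gives an explicit numerical threshold and condensing a text does not turn 9 into 10.

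The stage 1 point is weaker, and this also stands. Both sentences that set a stage 1 rule agree on stopping below 3. The more-than-3 phrase sits in a status report, and the section Interim analysis says that milestone has already been passed. If more than 3 patients did respond, stage 1 is passed on either reading. The rows with ≥ 4/30 therefore show what that wording would imply as a rule; no section prescribes it.

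It can also be said that other boundaries satisfy the limits: ≥ 2/30 with ≥ 9/65 gives 0.196 and 0.920. True, but no section states that rule. Finally, reaching the threshold only leads to phase III being considered, subject to safety, tolerability and feasibility. That limits the consequence, but a go/no-go rule still needs a single value.

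**Conclusion.** The concern holds. The article states the final success threshold in two incompatible ways, and they give opposite conclusions at exactly 9 responders: a chance of 7.7%, 12.1% or 5.4% at true rates of 10%, 15% or 20%. Among the rules the text can be read to give, only ≥ 3/30 with ≥ 9/65 meets both stated error rates (0.183 and 0.901). The Abstract's ≥ 10/65 has power 0.847, which is 5.3 percentage points below 90%. The attained 0.183 against a nominal 20% is ordinary discreteness and no error. The stage 1 wording in the Abstract's Discussion is a secondary misstatement that should not affect a decision already taken. These figures assume a one-sided 20% level, exact binomial counts, and 30 and 65 evaluable patients as planned.

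**What to change.** State one rule throughout: stop if 2 or fewer of the first 30 evaluable patients respond; regard the treatment as potentially effective if 9 or more of 65 respond.

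- In the Abstract's Methods paragraph, change the final threshold to nine or more of 65.
- In the Abstract's Discussion paragraph, change the stage 1 criterion to 3 or more of 30.
- Optionally, add the attained type I error (0.183) and power (0.901) to the sample size section, so that a reader can tie the rule to its error rates.

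The cost is a wording correction: sample size, conduct and analysis are unchanged. The article says stage 2 is still recruiting, so the correction can be dated before the final responder count is known.

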**Discussion:**

This study aims to investigate whether 6MP might be an effective treatment for BRCA deficient tumours even after the development of resistance to PARP inhibitors or platinum drugs. The study has surpassed the first stage analysis criteria of more than 3 out of 30 evaluable patients responding at 8 weeks, and is currently in the second stage of recruitment.

**Trial registration:**

NCT01432145http://www.ClinicalTrials.gov

## Background

Ovarian cancer is the fourth most common cause of cancer mortality in women; the majority (75%) of ovarian cancer patients will present with late stage disease (International Federation of Gynaecology and Obstetrics (FIGO) stage III/IV), and the overall prognosis remains poor with five year survival rates of 30- 40%. Current first line chemotherapy for ovarian cancer usually comprises of a combination of carboplatin and paclitaxel. Despite complete remissions in approximately 75% of patients, responses are generally short lived, with median progression-free survival (PFS) ranging from 16–21 months [1]. Despite initial response rates of 65-80% to first line chemotherapy, the majority of patients will relapse and ultimately develop resistance to further chemotherapy.

Breast cancer is the most common cancer in the UK; around 55,000 people are diagnosed each year. There are currently multiple options for the treatment of patients with advanced breast cancer, including hormone therapy, chemotherapy and Her-2-directed therapy, as well as possible radiotherapy and/or surgery for patients with symptomatic oligo-metastatic disease, thus most breast cancer patients with advanced stage disease will receive multiple lines of therapy.

BRCA1 and BRCA2 genes play an important role in homologous recombination DNA repair and have been implicated in familial breast and ovarian cancer syndromes. In addition to germline BRCA1/2 mutations, silencing of BRCA1/2 expression can also occur via epigenetic processes such as promoter hyper- methylation and this has been documented in 11-14% of breast cancers [2] and 11-35% of ovarian cancer patients [3].

For patients with metastatic cancer, the challenge is to develop better treatment strategies to maximise tumour cell kill and minimise toxicity. In patients with BRCA1/2 deficient cancers, one such approach has been to develop molecular targeted therapy using PARP inhibitors that selectively exploit biological pathways within tumour cells, which differ from those in normal cells and wider concepts of genetic synthetic lethality [4–6]. PARP is a nuclear enzyme activated in response to DNA single strand breaks and is involved in repair of these lesions via the base excision pathway (BER). The main lesions formed by cisplatin are intra-strand crosslinks between closely adjacent purine bases [7]. Efficient BER is also required for repair of these lesions. An inability to couple DNA damage to an apoptotic signal pathway may lead to the development of resistance to platinum and PARP inhibitors. Tumours may also acquire resistance by additional mutations in the BRCA1 & BRCA2 gene [8–10] and so there is a place for further investigation of DNA repair inhibition in HR defective tumours.

Carriers of BRCA mutations have an increased lifetime risk of developing breast or ovarian cancer and in these families the focus has been on prevention (screening for early detection or prophylactic surgery). Hitherto, once cancers have developed in these patients they have generally received standard therapy for that tumour type. However patients with a BRCA1/2 mutation have an increased sensitivity to agents that cause DNA damage through double stranded breaks or DNA cross-links, such as platinum agents due to the genetic basis of their tumours. Recent clinical studies with cisplatin based chemotherapy and PARP inhibitors have sought to exploit the genetic basis of these tumours in order to develop a more tailored approach to therapy for patients with breast and ovarian cancer and known BRCA mutations and/or suspected defects in homologous recombination (defined as patients with triple receptor negative (oestrogen, progesterone and HER2 receptor-negative) breast cancer, or advanced high grade serous ovarian cancer with a history of repeated platinum sensitivity).

The thiopurines 6-mercaptopurine (6MP) and 6-thioguanine (6TG) are growth inhibitory antimetabolites licensed for the treatment of acute leukaemias and also chronic granulocytic leukaemia. Structurally, these agents are purine analogues that interfere with nucleic acid biosynthesis. Methotrexate is also an antimetabolite and inhibits tetrahydrofolate dehydrogenase and prevents formation of tetrahydrofolate, which is required for synthesis of thymidylate, an essential component of DNA. It is routinely used in combination with 6MP in patients with ALL as it has been shown to reduce de novo purine synthesis and thus enhance the cytotoxicity of 6MP by promoting its conversion to 6TGNs [11, 12]. Methotrexate has also been widely used in the treatment of a number of solid tumours such as breast, ovarian, lung and cervical cancers. Furthermore a recent synthetic lethality screen has identified methotrexate as an agent that has activity in DNA mismatch repair (MMR) defective cancers, as evidenced by its selective toxicity in cells lacking functional mutS homolog 2 (MSH2) gene mutations [13].

The rationale for our study is based on in-vitro work by Issaeva et al. [14] who have shown that 6- thioguanine (6TG) selectively kills BRCA2-defective cells as effectively as the PARP inhibitor, AGO14699. Even after cells have acquired resistance to a PARP inhibitor or cisplatin, they retain sensitivity to 6TG. However as long term administration of 6TG is problematic due to dose related toxicities, such as veno- occlusive disease, this study will assess the activity of 6-mercaptopurine (6MP), which is converted to the same active moiety, 6-thioguanine nucleotide, prior to incorporation into DNA. Low dose methotrexate will be used in combination with 6MP in this study as it promotes the formation of thioguanine nucleotides.

### Objectives

The primary objective of the 6MP study is to determine the objective tumour response rate to 6-mercaptopurine (6MP) and low-dose methotrexate in patients with previously treated breast, ovarian, fallopian tube or primary serous peritoneal cancer who are known to have a BRCA mutation, 8 weeks after starting treatment. Secondary objectives include progression-free survival (PFS), overall survival (OS), safety, toxicity, pharmacokinetics; and quality of life. Exploratory objectives include evaluation of patients’ Mismatch Repair (MMR) status at initial diagnosis, prior to starting the study, and after 7 weeks of treatment. An assessment of the feasibility of this trial in a multi-centre context will be used to inform the case for a follow-on phase III study.

## Methods

### Study design

The 6MP study is a single arm, non-randomised, two-stage, multi-centre Phase II trial. The trial opened in June 2011 and recruits from 14 centres across the UK. Following written informed consent and screening tests, eligible patients will commence treatment, taking 6MP once daily and methotrexate once weekly. Treatment will continue until disease progression or unacceptable toxicity. Conduct of the 6MP trial complies with the ethical principles of the Declaration of Helsinki (1996) and the regulatory requirements for clinical trials of an investigational medicinal product under the European Union Clinical Trials Directive. The study has been approved by the National Research Ethics Service (NRES) Committee South Central – Oxford B (REC reference 10/H0605/79).

The trial is sponsored by the University of Oxford, with funding from Cancer Research UK’s Clinical Trials Award and Advisory Committee (CTAAC) who approved a full funding application on 26th October 2010, and this work was supported by the Oxford Partnership Comprehensive Biomedical Research Centre with funding from the Department of Health’s National Institute of Health Research (NIHR) Biomedical Research Centre funding scheme.

Data submission for the 6MP trial is via electronic submission into the online database system OpenClinica by site staff, and this is closely monitored. The Oncology Clinical Trial Office (OCTO) coordinates the trial, and OCTO staff are in charge of the day-to-day running of the trial, as well as managing the trial as a whole; organising trial meetings, completing trial documentation, site monitoring, and database management. All statistical analysis will be undertaken by statisticians at the Centre for Statistics in Medicine (CSM) at the University of Oxford.

### Participants

To be eligible for inclusion in the 6MP study, patients must be aged 18 or older, have proven BRCA1 or BRCA2 mutations, and have measurable disease as defined by RECIST v1.1 criteria. For breast cancer patients, patients must have locally advanced or metastatic breast cancer, and may have received up to 3 previous lines of chemotherapy in the locally advanced or metastatic setting. Ovarian, fallopian tube or primary serous peritoneal cancer patients must have disease that is either platinum resistant or in whom further platinum based therapy is inappropriate. All patients must have an Eastern Cooperative Oncology Group (ECOG) performance score between 0 and 2, a life expectancy of greater than 12 weeks, and adequate haematological and biochemical function. Patients are excluded from participating in the study if they have a Low/Low genotype on Thiopurine methyltransferase (TPMT) testing. Patients with low activity (10% prevalence) or especially absent activity (prevalence 0.3%) are at a heightened risk of drug-induced bone marrow toxicity due to accumulation of the unmetabolised 6MP. At the start of the trial, patients were excluded from participation if they had low TPMT activity (<68 U/ml), but a decision was made by the 6MP TMG in October 2013 to remove this exclusion as a substantial amendment to the protocol, as evidence suggested that moderate TPMT activity levels did not affect dose intensity or levels of myelosuppression seen. Patients were already being closely monitored in the first cycle therefore no additional monitoring was implemented for this patient group. A total of 14 sites across the UK are actively recruiting for this trial; Royal United Hospital, Bath; Belfast City Hospital, Belfast; Velindre Hospital, Cardiff; University Hospital, Coventry and Warwickshire; Western General Hospital, Edinburgh; Guy’s Hospital, London; Royal Marsden Hospital, London; University College London Hospital, London; Christie Hospital, Manchester; Freeman Hospital, Newcastle; Mount Vernon Hospital, Middlesex; Churchill Hospital, Oxford; Royal Marsden Hospital, Sutton; Clatterbridge, Wirral.

### Interventions

Patients in the trial are treated with 6-mercaptopurine (6MP) and methotrexate continuously in 28 day cycles until disease progression or unacceptable toxicity. The dose of 6MP given is 55 mg/m^2^ body surface area, administered orally once a day at least one hour after eating; tablets should be taken at roughly the same time each day. A 15 mg/m^2^ dose of methotrexate should be taken orally once a week in the morning. It should be noted that these starting doses are not those originally set at the beginning of the trial. Doses were originally 75 mg/m^2^ of 6MP daily, and 20 mg/m^2^ of methotrexate weekly, but these were reduced following an Urgent Safety Measure in August 2012 due to a large proportion of patients requiring a dose reduction or treatment delay due to incidences of myelosuppression. Although myelosuppression is an expected toxicity of these agents and the Internal Safety Committee did not have serious safety concerns, the Trial Management Group concurred that a dose reduction was indicated to ensure dose intensity could be maintained without compromising patient safety.

### Outcomes and assessments

The primary outcome of the 6MP study is objective response, defined as complete response (CR), partial response (PR), or stable disease (SD), as measured by radiological disease response using RECIST criteria version 1.1. Patients who yield progressive disease (PD) are classed as non-responders. Tumour size is measured radiologically with computerised tomography (CT) and/or magnetic resonance imaging (MRI); the same method is used at baseline and at follow-up. The first time point for this primary analysis is 8 weeks after first treatment.

Secondary outcome measures include safety, overall survival (OS) and progression-free survival (PFS). Length of overall survival is defined in whole days as the time from entry into the study until death from any cause, and those patients who are not observed to die during the course of the trial will be censored at their last known follow-up date. Length of progression-free survival is defined in whole days as the time from entry into the study until progression or death from any cause, and those patients who are not observed to progress or die during the course of the trial will be censored at their last known progression- free follow-up date. Grade 3 or 4 Adverse Events (AEs), as defined by the National Cancer Institute (NCI) Common Terminology Criteria for Adverse Events (CTCAE) version 4.0, and abnormal clinical and laboratory findings will be collected at regular follow-up visits throughout the trial in order to evaluate safety. Pharmacokinetics are measured by the assessment of red blood cell 6-thioguanine nucleotide (6TGN) levels using a validated high-performance liquid chromatography (HPLC) assay, and the effect of pharmacogenomics on thiopurine metabolism is measured by assessing the TPMT genotype using a validated assay. Another secondary outcome is quality of life, which is evaluated using the EQ-5D questionnaire at baseline, 3 and 6 months, and at the end of treatment or 12 months, as well as using the ECOG performance status measure after each cycle.

Recruitment is monitored throughout the trial, in order to assess the feasibility of the 6MP study as a multi- centre study. If each site recruits 3–4 patients per year, this indicates that a large randomised phase III study would be feasible. The exploratory outcome measure of the 6MP trial is the Mismatch Repair (MMR) status of each patient; this will be assessed using validated immunohistochemical/MSI assays using tissue from initial diagnosis, just prior to starting the study, and after 7 weeks of treatment, as well as from optional extra biopsies.

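### The primary outcome counts stable disease as response, but the 10%/20% rates and the 3/30 and 9/65 cut-offs are given without a basis on that scale, so the stated 20% error is not secured

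*Protocol article*

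**What the plan says.** - **Outcome.** Outcomes and assessments sets the primary outcome as "objective response, defined as complete response (CR), partial response (PR), or stable disease (SD), as measured by radiological disease response". It adds: "Patients who yield progressive disease (PD) are classed as non-responders". The abstract (Methods) agrees: "The primary outcome is objective response at 8 weeks, defined by RECISTS v1.1 as complete response, partial response or stable disease". The definition is therefore deliberate and not a slip in one place.
- **Objective.** Objectives describes the aim differently, as to "determine the objective tumour response rate to 6-mercaptopurine (6MP) and low-dose methotrexate", at 8 weeks.
- **Design.** Sample size determination and power uses a Simon admissible two-stage design "to detect an increase in response rate from 10% to 20%, with a power of 90% and a significance level of" 20%. The trial stops if fewer than 3 of 30 evaluable patients respond. The treatment is regarded as potentially effective if nine or more of 65 respond. The abstract requires more than nine.
- **Reporting.** Statistical analysis plans to report CR, PR, SD and PD separately as well, but the decision rule uses the combined count.
- **Status.** Interim analysis and the abstract's Discussion state that stage 1 has been passed and stage 2 is recruiting.

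**The concern.** Counting stable disease turns a tumour-shrinkage outcome into the absence of progression at 8 weeks. The name, the objective and the 10%/20% rates all read as though they belong to shrinkage. No section gives a basis for either rate on the non-progression scale, and no section gives a non-progression rate for an inactive regimen.

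Both decision points depend on this. If more than 10% of patients on an inactive regimen would be free of progression at 8 weeks, the futility rule stops too rarely. The final rule then labels the treatment potentially effective more often than the stated 20%. Passing stage 1, which the article presents as a milestone, would then say little about activity.

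**Working it through.** **Inputs from the article.** n1 = 30 and N = 65 (35 in stage 2); continue if X1 ≥ 3; success if X1 + X2 ≥ 9; p0 = 0.10, p1 = 0.20; significance level 20%, power 90% (all from Sample size determination and power). A responder is CR, PR or SD (Outcomes and assessments).

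**Input not in the article.** The true 8-week CR+PR+SD rate under an inactive regimen. It is treated as an assumption and shown over a range.

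**Step 1: formula.**

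P(go | p) = Σ over x1 = 3 to 30 of Bin(x1; 30, p) × P(X2 ≥ 9 − x1), with X2 ~ Bin(35, p).

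**Step 2: reproduce the plan's own figures.**

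- p = 0.10: P(go) = 0.183, within the 20% level; P(stop at stage 1) = 0.411.
- p = 0.20: P(go) = 0.901, meeting the 90% power.

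The arithmetic for 10% against 20% is correct. The question is only whether those rates belong to this outcome.

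**Step 3: read the rates on the outcome's own scale.** Only PD is a non-response, so P(progressed by 8 weeks) = 1 − p. That is 90% under the null and 80% under the target. As an illustration, under a constant hazard the median time to progression is 8 × ln 2 / (−ln p):

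- p = 0.10: 5.545 / 2.303 = 2.4 weeks
- p = 0.20: 5.545 / 1.609 = 3.4 weeks
- p = 0.25: 5.545 / 1.386 = 4.0 weeks
- p = 0.50: 5.545 / 0.693 = 8.0 weeks

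**Step 4: apply the same rule at other true rates.**

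| True 8-week CR+PR+SD rate | P(stop at stage 1) | P(go), ≥9/65 | P(go), >9/65 (abstract) |
|---|---|---|---|
| 10% | 0.411 | 0.183 | 0.106 |
| 15% | 0.151 | 0.622 | 0.500 |
| 20% | 0.044 | 0.901 | 0.847 |
| 25% | 0.011 | 0.982 | 0.971 |
| 30% | 0.002 | 0.997 | 0.996 |
| 40% | <0.001 | >0.999 | >0.999 |

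At 15%, the error is 0.622 / 0.20 = 3.1 times the stated level. The abstract's stricter cut-off does not change the picture.

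**Step 5: what a rule on the non-progression scale could look like at 30/65.** The rates here are illustrative and have no source in the article.

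- 30% vs 45%: continue at ≥10/30, success at ≥23/65; alpha 0.168, power 0.907.
- 40% vs 55%: continue at ≥12/30, success at ≥30/65; alpha 0.174, power 0.923.

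Both widen the detectable difference from 10 to 15 points. Keeping 10 points at 30/65 with alpha ≤ 0.20 gives power of at most about 0.78 (30% vs 40%) or 0.77 (40% vs 50%).

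**The case against.** **The key rate is missing.** A reader might infer that an inactive regimen would almost surely be declared potentially effective. The article does not support that as an unconditional statement, because it gives no 8-week non-progression rate for an inactive regimen. The inference needs a true rate of about 25% or more. This objection stands, and the claim must stay conditional. It does not rescue the rule, because the error is already 0.62 at 15%.

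**The plan does not contradict itself on progression rates.** One might cite the eligibility requirement of life expectancy above 12 weeks, the 28-day cycles, the EQ-5D schedule or the 1- and 2-year PFS summaries as proof that 90% progression by 8 weeks is impossible. They are context, not proof. Life expectancy concerns death, treatment simply continues until progression or unacceptable toxicity, the last EQ-5D time point allows for the end of treatment, and the PFS summaries are descriptive. The medians in weeks also rest on a constant hazard. This objection stands too.

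**There are safeguards.** Phase III is only to be considered, and only if the treatment is also safe, well tolerated and feasible to roll out. The four response categories will be reported separately. This limits the harm, but the label of potentially effective follows from the combined count alone, so the safeguards do not repair the rule.

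**The remedy is late.** Stage 1 has been analysed in a single-arm trial, so any change of outcome or boundary is open to the charge of being data-driven. This stands and is dealt with in the fix.

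**Conclusion.** The point holds as a mismatch between the primary outcome and the rates and cut-offs used to judge it. The outcome is 8-week non-progression. The 10% and 20% rates are unsupported on that scale and imply 90% and 80% progression by 8 weeks. The calculation is right for its stated inputs, but the 20% error applies only if an inactive regimen leaves 10% of patients non-progressive.

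The size depends on an assumed rate. The probability of a positive declaration is 0.62 at 15%, 0.90 at 20%, 0.98 at 25% and above 0.99 from 30% upwards. At 25% or more, stage 1 is passed with probability of at least 0.98, so passing it would be weak evidence of activity. The documents do not establish which of these rates applies, so they do not show that a false-positive result is near certain. They show that the stated error control is unsecured. Because this is the trial's primary decision rule, it should be corrected before the final analysis.

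**What to change.** **Preferred.** Apply the 10%/20% design, with its cut-offs of 3/30 and 9/65, to CR+PR, and state the basis for those rates. Rename CR+PR+SD as disease control at 8 weeks and report it as a secondary outcome. Report the stage-1 count split into CR/PR and SD, and say how the trial proceeds if the CR+PR count falls below 3 of 30. Align the abstract's final cut-off with the Methods: nine or more gives power 0.901, more than nine gives 0.847.

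**If CR+PR+SD stays primary.** Restate and justify p0, p1 and both cut-offs for non-progression. The 30% vs 45% and 40% vs 55% rules above show what fits 30/65. State openly that the detectable difference becomes 15 points, or enlarge the trial to keep 10.

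**Cost.** A protocol and analysis-plan amendment. No extra scans are needed, since the four categories are already planned for reporting, and no extra patients unless a 10-point difference is kept on the non-progression scale. The change follows the stage-1 analysis, so it must be dated and disclosed as post-interim, and the result under the present rule must be reported beside the new one. Under the preferred option the headline rate will look less favourable.
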